**Health care use, costs and quality of life**	
Societal costs [60]	Including general practitioner visits, outpatient visits, hospital days, rehabilitation center days, nursing home days, physiotherapy use, home care, (change in) medication use, informal care, costs for patients related to RA/axSpA, work situation and productivity related costs. Similar questionnaires have been used in previous studies on physiotherapy in inflammatory arthritis
EuroQol (EQ‐5D‐5L) [61, 62]	The EuroQol is a standardized instrument including 5 dimensions of health (mobility, selfcare, daily activities, pain/complaints and anxiety/depression), resulting in a score anchored at 0–1, with a higher score indicating better health. It also includes a ‘thermometer’, a visual analog scale with a score ranging from 0 (worst possible health) to 100 (perfect health)
**Expectancy of treatment and global perceived effect**	
Expectancy of intervention	One question constructed by the research group to ask the participant to what extent they expect the intervention to effect their work ability. On a NRS scale ranging from 0 (not at all) to 10 (very)
GPE (Global Perceived Effect)	Contains the anchor question on the perceived effect: “Has the vocational PT-led intervention changed your daily functioning?”

^a^Measured only in the study population of axial spondyloarthritis patients

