### Intervention

#### Recruitment and training of PTs

The intervention will be delivered by primary care PTs in the neighbourhood of the participants’ home. PTs will be primarily recruited from the ‘ReumanetNL’ network (www.reumanetnl.nl), a nationwide network of PTs with expertise in treating people with RA or axSpA. Participants in the experimental group who prefer to be treated by the PT that they are familiar with, are given this opportunity if this PT is willing to follow the study training and consent with the treatment protocol. To minimize contamination and because its (cost-)effectiveness is still unknown, PTs in the experimental arm are prohibited to provide the experimental intervention to participants outside the study and to participants in the control arm during their participation in the study.

Participating PTs are instructed to comply with the current Dutch physiotherapy guidelines for RA [33] and physiotherapeutic management recommendations for axSpA [34]. In addition they will have access to an online training environment and receive the treatment protocol on paper. The mandatory training for PTs will consist of multiple e-learnings on i) integration of work in the physiotherapy treatment, ii) Dutch occupational healthcare system and work-related laws/regulations, and iii) treatment protocol including a live question session. If deemed necessary, supplemental disease-specific trainings could be followed. The total duration of this mandatory training is approximately five hours. Participating PTs can contact a study team member with extensive expertise in physiotherapy for these populations at any time during the trial.

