### Control

The control group will continue their usual care.

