### Outcome measures and data collection

The primary outcome is the participants’ reported work ability assessed by the Work Ability Index-Single Item Scale (WAS) [31]. The secondary outcomes are divided into four categories: 1) work-related outcomes; 2) clinical outcomes; 3) healthcare use and costs from the societal perspective and 4) expectancy of the treatment and global perceived effect. A detailed description of all outcome measures is shown in Table 3 and the timepoints on which they are assessed are displayed in Table 4.

**Table 3 Tab3:** Description of outcome measures

Measures	Description

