### Statistical analysis

#### Primary analysis

A multilevel, regression analysis – with levels of patient and time point – will be performed using linear mixed modeling. Primary outcome measure WAS will be analyzed as a dependent variable, using the study group (intervention vs control), stratification variables (i.e., disease (RA vs. axSpA), disease duration (< 5 vs. > 5 years), current sick leave at randomization (yes or no)) and other potential confounders as independent variables. All analyses will be performed according to the intention-to-treat principle. Statistical significance will be accepted at *p*-values of less than 0.05 (two-sided testing).

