#### Secondary analysis

Similar analyses will be performed for the secondary time points T3 and T6, as well as for the total follow-up period, and with all secondary outcome measures. Only Global Perceived Effect (GPE) will be analyzed as a dichotomous variable (‘completely recovered’ and ‘much recovered’ vs. all other responses) using logistic multilevel analysis. Furthermore, effect sizes from all clinical outcome measures will be calculated.

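### The GPE question as printed asks about the experimental intervention, so the planned between-arm GPE odds ratio would be biased towards that arm to an unknown degree

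*Protocol article*

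**What the plan says.** Under Outcome measures and data collection, the fourth category of secondary outcomes is "4) expectancy of the treatment and global perceived effect". Table 3 states the GPE anchor: "Has the vocational PT-led intervention changed your daily functioning".

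The Secondary analysis section says "Similar analyses will be performed for the secondary time points T3 and T6, as well as for the total follow-up period", and extends this to every secondary outcome. GPE is singled out only for its scale: "Only Global Perceived Effect (GPE) will be analyzed as a dichotomous variable". The split is given as "completely recovered’ and ‘much recovered’ vs. all other responses) using logistic multilevel analysis". The model being carried over is in the Primary analysis section, where WAS is regressed "using the study group (intervention vs control), stratification variables" and other potential confounders.

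On the comparator, the Control section says "The control group will continue their usual care". The section on recruitment and training of physiotherapists (PTs) adds that, while they take part, therapists who deliver the intervention are "prohibited to provide the experimental intervention to participants outside the study and to participants in the control arm". The Randomization and blinding section says that participants cannot be blinded.

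**The concern.** A between-arm comparison needs a question that means the same thing in both arms. This one asks participants to attribute change to a named treatment that, by plan, only one arm receives. A control participant whose functioning improved a great deal under usual care has no clear way to say so. The honest answers are that the intervention changed nothing, or no answer at all.

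Part of any arm difference in GPE could therefore come from the wording and not from how participants fared. A favourable GPE odds ratio might then be cited as support for the intervention when it carries little information. If many controls leave the item blank, the comparison rests on a selected remainder.

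A second, smaller problem is that the stem asks about change in daily functioning while the responder definition uses degrees of recovery.

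**Working it through.** **1. Is GPE compared between arms?** No sentence says so outright. It follows from three statements: GPE is listed as a secondary outcome; all secondary outcomes get analyses similar to the primary one; and the primary model has study group as an independent variable. GPE is exempted from the linear form only.

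**2. Is GPE limited to the intervention arm?** Nothing printed says so. The only GPE restriction among the Table 4 footnotes concerns timing: it is not asked at baseline. Where Table 3 limits a measure to a subset it says so, as with the BASFI footnote for axial spondyloarthritis. GPE carries no such mark. The body of Table 4 is not shown, so an arm-specific mark there cannot be fully excluded.

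**3. Stem against responder labels.** The stem concerns whether daily functioning changed. The two success labels describe complete or much recovery. A participant can report a large change without having recovered.

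**4. The plan's own numbers.** The article gives no GPE rate or GPE sample size. For WAS, with difference 8 − 7 = 1, SD 2, two-sided alpha 0.05 and power 0.80:

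- n per arm = 2 × (2/1)² × (1.96 + 0.8416)² = 62.8, rounded up to 63, so 126 in total.
- 126 / 0.90 = 140.

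Both figures agree with the article. The 63 per arm is used below only as a realistic number of evaluable participants.

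**5. How much could wording alone do?** Suppose functioning is the same in both arms and any gap in GPE responders comes from the wording. Using a two-sided two-proportion test at one time point:

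P(significant) = Φ[(d − 1.96 × se0) / se1], where d = p1 − p2, se0 = √[p̄(1 − p̄) × 2/63] and se1 = √{[p1(1 − p1) + p2(1 − p2)]/63}.

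- p1 = 10%, p2 = 0%: p̄ = 0.05, se0 = 0.0388, se1 = 0.0378. (0.10 − 0.0761)/0.0378 = 0.63, giving 0.74.
- p1 = 10%, p2 = 5%: p̄ = 0.075, se0 = 0.0469, se1 = 0.0467. (0.05 − 0.0920)/0.0467 = −0.90, giving 0.18.

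| Intervention responders (assumed) | Controls 0% (assumed) | Controls 5% (assumed) |
|---|---|---|
| 10% | 74% | 18% |
| 20% | 97% | 73% |
| 30% | >99% | 97% |

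**6. Exact check of the extreme column.** With 0/63 control responders, two-sided Fisher p is 0.058 for 5/63 and 0.028 for 6/63 in the intervention arm, so six responders are enough. The binomial chance of six or more out of 63 at a true rate of 10% is 61%. The normal approximation (74%) is therefore somewhat generous at such low rates, but the pattern is the same.

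These are single-visit 2×2 calculations, not the planned multilevel logistic model. They show sensitivity to the control rate and do not predict the trial's result.

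**The case against.** The strongest reply is that this is a condensed article. It prints one English sentence for an item presumably asked in Dutch, shows neither the questionnaire nor the full response scale, and its schedule table is a figure that is not shown. A neutral control-arm wording, or routing of the item by arm in the online questionnaire, may exist in the full protocol. That stands as a reason for caution about what participants were actually asked. It does not remove the conflict between the wording the article chose to print and the analysis it states. If a neutral version exists, Table 3 misdescribes the item; if GPE is asked in one arm only, the Secondary analysis section describes a comparison that cannot be run.

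The second reply concerns size, and most of it stands. A reader might infer that control responders must be zero, so that GPE merely records who was allocated to the intervention. The document does not support that. The responder labels describe recovery, and a control participant could endorse much recovered by rating their own state. Zero control responders is thus a worst case. Moving controls from 0% to 5% takes the first row of the table from 74% to 18%. Separation in the logistic model, meaning no finite estimate for the group effect, likewise arises only with zero or near-zero control events.

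Third, the mismatch between stem and labels may be loose labelling or translation, since the options are never printed beside the stem. That is fair; it needs confirming.

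**Conclusion.** The point holds in limited form. As printed, the GPE stem and the planned between-arm analysis do not fit together. The direction of bias is towards the intervention arm; its size is unknown, because the article gives no GPE rates and the percentages above rest entirely on assumed ones. The conclusion also rests on the printed wording being what both arms were asked, and on reading similar analyses as including the study-group term, which is the only reading the text supports.

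It should be fixed, but it does not threaten the trial. A reader might infer that the main conclusions are compromised, and they are not. The primary outcome and the sample size rest on WAS, the economic evaluation uses EQ-5D-5L and costs, and no other stated analysis depends on GPE.

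**What to change.** First, confirm which wording and response scale each arm was given. If a neutral control-arm wording was used, correct Table 3 to state it, together with the response options.

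If the printed wording was used in both arms:

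- From now on, use one arm-neutral anchor on the stated construct in both arms, for example: *Compared with the start of the study, how has your daily functioning changed?* Give it response options that match the stem, and define a responder on those options.
- For answers already collected on the printed wording, report GPE descriptively in the intervention arm only and drop the between-arm test.
- Do not pool answers to the two wordings. The article says the trial is ongoing, so a change now would otherwise mix versions across participants and visits.

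The cost is a minor questionnaire amendment and, for data already collected, the loss of one secondary comparison.

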**Table 4 Tab4:**
[figure not shown]
SPIRIT flowchart: Outcome measures at the different timepoints

^a^The PSC NRS will not be measured at T3 and T6

^b^The expectancy of the treatment will only be measured at T0

^c^The GPE will not be measured at T0

At baseline, disease characteristics will be retrieved from the participants’ rheumatologist. Data from patient questionnaires will be collected and stored in the online database OnlinePROMS© (2020, Interactive Studios BV, Rosmalen, the Netherlands).

#### (Serious) Adverse events

All participants and PTs will be asked to immediately and proactively report serious adverse events (SAE) or adverse events (AE) to the researchers. SAEs and AEs, directly related to the intervention, will be recorded and followed until they have abated, or until a stable situation is reached. The researchers will report all intervention-related SAEs to the sponsor without undue delay after obtaining knowledge of the events.

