### Randomization and blinding

Randomization will be performed by the researcher (NB) using the software Castor (Castor. EDC©) at the participant level, in blocks of varying sizes (2–4-6 participants, with block size randomization) in a 1:1 ratio. Randomization will be stratified for disease (RA vs. axSpA), disease duration (< 5 vs. ≥ 5 years since diagnosis), and current sick leave (yes vs. no). We will stratify for disease duration because in the first few years after the diagnosis pharmacological treatment has started and symptoms could possibly fluctuate more than later in the disease course. The researcher will not be blinded for treatment allocation of the participants due to logistic reasons regarding contact with participants and treating PTs, but the researchers conducting the primary analyses will be blinded for the group allocation.

After completion of the baseline assessment, the participants will be informed by the researcher (NB) about their assigned condition (intervention/control). Given the nature of the intervention, participants and PTs involved in the treatment cannot be blinded to the treatment allocation.

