#### Process evaluation

The process of the trial will be evaluated both quantitatively and qualitatively, comparable to previous and ongoing other trials from our group [63, 64]. For the quantitative evaluation, PTs will report process parameters after each treatment session (in OnlinePROMS®), including participant adherence, number of treatment sessions, the content of the applied treatment, and adverse events. Based on these parameters, PT treatment fidelity can be assessed. For the qualitative evaluation, a random sample of 10 participants and 10 PTs will be selected and invited for semi-structured interviews to discuss experiences, barriers and facilitators with regard to the intervention. The semi-structured interviews will be conducted after the selected participant has completed the 12-month assessment.

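### Formal adverse event records cover in effect one arm only, so adverse event counts cannot be compared between arms

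*Protocol article*

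**What the plan says.** Three statements in the protocol article's section on (serious) adverse events set the rule.

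- Reporting is open to both arms: "All participants and PTs will be asked to immediately and proactively report serious adverse events (SAE) or adverse events (AE) to the researchers".
- Recording and follow-up are conditional: "SAEs and AEs, directly related to the intervention, will be recorded and followed until they have abated".
- Onward reporting carries the same condition: "The researchers will report all intervention-related SAEs to the sponsor without undue delay after obtaining knowledge of the events".

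A second source appears under Process evaluation. After each session PTs enter process parameters, "including participant adherence, number of treatment sessions, the content of the applied treatment, and adverse events". No relatedness condition is stated there.

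On the comparator, the Control section says: "The control group will continue their usual care". The section on recruitment and training of PTs bars study PTs from giving the experimental intervention to control participants while they are in the study. On blinding, the Randomization and blinding section says: "The researcher will not be blinded for treatment allocation of the participants". That section adds that participants and treating PTs cannot be blinded either, and that those running the primary analyses will be.

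**The concern.** Relatedness to the intervention is normally an attribute given to an event that is already on record. Here it is the condition for being recorded and followed. In a trial against usual care that condition can be met in one arm only, so controls are asked to report events for which the article provides no record.

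This matters because the population has rheumatoid arthritis or axial spondyloarthritis, with joint pain, stiffness and fatigue as core features, and the intervention includes exercise therapy of gradually increasing intensity. For one participant it is hard to say whether a flare or a rise in pain comes from the disease or from the exercise. A randomized control rate is the natural way to settle that at group level, and the stated rule discards it. What would be left for the trial report is a list of intervention-arm events with no comparator.

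**Working it through.** The point rests on reading the sections together. Arithmetic only illustrates it.

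**Step 1: which events enter each record**

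| Source | Relatedness condition | Intervention arm | Control arm |
|---|---|---|---|
| Reports to the researchers, (Serious) Adverse events section | Directly related to the intervention | Related events recorded | None can qualify, apart from crossover |
| PT log after each session, Process evaluation section | None stated | Recorded, over 10 to 21 sessions | No study sessions, so no log |

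Neither row yields a control-arm event.

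**Step 2: is the restrictive reading right?** The commas around the relatedness phrase leave a little room for doubt. The next sentence limits sponsor reporting to intervention-related SAEs, which supports reading the phrase as a restriction.

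**Step 3: arm size.** The Sample size calculation section gives a difference of 8 − 7 = 1 point, SD 2, two-sided alpha 0.05 and power 0.80.

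- n per arm = 2 × (1.960 + 0.842)² × 2² / 1² ≈ 62.8, rounded up to 63, so 126 in total.
- 126 / 0.90 = 140, or 70 per arm.

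The stated figures reproduce. They are used here only as the denominator.

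**Step 4: illustration.** The documents give no event rates, so these inputs are assumptions: the same all-cause AE risk in both arms, from 10% to 40%, and 10% to 50% of intervention-arm events judged directly related.

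- True events per arm: 70 × 0.10 = 7 up to 70 × 0.40 = 28, equal in the two arms.
- Recorded under the AE rule, intervention arm: 7 × 0.10 = 0.7 up to 28 × 0.50 = 14.
- Recorded under the AE rule, control arm: 0 throughout.
- If the PT log also caught every intervention-arm event, that arm's count would be 7 to 28, still against 0.

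With no true difference at all, the recorded counts could thus show anything from about 1 against 0 to 28 against 0. The control zero is a product of the definition, so a risk difference or ratio formed from these counts has no meaning.

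**The case against.** The strongest case against has four parts.

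1. **The trial sets no safety question.** The aim is effectiveness and cost-effectiveness, safety is not among the four secondary outcome categories, and no between-arm safety test is planned. This is true. It limits the weight of the point, since no promised analysis is defeated. It does not make one-sided harms data usable.

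2. **Other data are collected without a relatedness filter.** Pain and fatigue scores, physical function, absenteeism, hospital days, other healthcare use and medication changes come from participant questionnaires. A reader might infer that no comparative statement about harm is possible. That goes too far: these measures allow an indirect comparison. They do not identify or classify events, so they do not replace AE counts.

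3. **Stronger readings of the recording process are not in the text.**
   - A reader might infer that an event attributed to the disease is never recorded. The PT log states no such filter, so in the intervention arm it may be.
   - A reader might infer that PTs actively solicit events. The article says only that they report them after each session.
   - A reader might infer that unblinded staff judge relatedness when an event is reported. The article does not say who judges or when. It says only that the researcher in contact with participants and PTs is unblinded.
   - Nor are controls left without any request, since all participants are asked to report.

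4. **This is a condensed article.** Forms, definitions and causality assessment usually sit in the full protocol, and the assessment schedule (Table 4) is not visible here. Silence on those matters would be no finding. The recording condition, however, is stated outright, and the point concerns that statement.

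**Conclusion.** The concern holds in a limited form. As written, the article provides for formal AE and SAE records in the intervention arm and for none in the control arm, apart from crossover. Formal AE and SAE counts cannot be compared between arms, and an intervention-arm flare or pain increase has no control rate beside it. The control count is 0 of 70 by construction. The size of any resulting distortion cannot be derived from the documents, and the range in the working is illustrative.

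The primary work-ability result and the cost-utility result are unaffected. The conclusion assumes the restrictive reading of the recording sentence and assumes that no unseen document provides for control-arm recording. If one does, the article's sentence needs to be brought into line with it.

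**What to change.** Reword the (Serious) Adverse events section so that:

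- all reported SAEs, and AEs of prespecified types (for example flare, injury, or pain increase leading to care or sick leave), are recorded in both arms;
- they are collected with identical items in the online questionnaires already sent at 3, 6 and 12 months;
- relatedness is coded afterwards as a separate field and is not a condition of entry;
- the by-arm table uses this common questionnaire source only, with PT-logged events listed separately because they exist in one arm.

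The article says the study is still ongoing. If the questionnaires can no longer be changed, keep every event that participants in either arm have reported, and state in the report that counts of related events are not comparable by arm.

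The cost is a few extra questionnaire items, a minor amendment and slightly more recording work. The change affects data capture only.
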